## Abstract

**Background: **Typhoid and paratyphoid fever (enteric fever) is a common cause of non-specific febrile infection in adults and children presenting to health care facilities in low resource settings such as the South Asia.  A 7-day course of a single oral antimicrobial such as ciprofloxacin, cefixime, or azithromycin is commonly used for its treatment. Increasing antimicrobial resistance threatens the effectiveness of these treatment choices. We hypothesize that combined treatment with azithromycin (active mainly intracellularly) and cefixime (active mainly extracellularly) will be a better option for the treatment of clinically suspected and culture-confirmed typhoid fever in South Asia.

**Methods:** This is a phase IV, international multi-center, multi-country, comparative participant-and observer-blind, 1:1 randomised clinical trial. Patients with suspected uncomplicated typhoid fever will be randomized to one of the two interventions: Arm A: azithromycin 20mg/kg/day oral dose once daily (maximum 1gm/day) and cefixime 20mg/kg/day oral dose in two divided doses (maximum 400mg bd) for 7 days, Arm B: azithromycin 20mg/kg/day oral dose once daily (max 1gm/day) for 7 days AND cefixime-matched placebo for 7 days. We will recruit 1500 patients across sites in Bangladesh, India, Nepal, and Pakistan. We will assess whether treatment outcomes are better with the combination after one week of treatment and at one- and three-months follow-up.

**Discussion:** Combined treatment may limit the emergence of resistance if one of the components is active against resistant sub-populations not covered by the other antimicrobial activity. If the combined treatment is better than the single antimicrobial treatment, this will be an important result for patients across South Asia and other typhoid endemic areas.

**Clinicaltrials.gov registration:** NCT04349826 (16/04/2020)

## Introduction

Typhoid (caused by
*Salmonella enterica* serovar Typhi) and paratyphoid fever (caused by
*Salmonella enterica* serovar Paratyphi A), collectively referred to as typhoid fever in this protocol, are common causes of non-specific febrile infection in adults and children presenting to health care facilities in low resource settings such as the South Asia region
^
1–
4
^. South Asia has been described as the largest hub for typhoid fever in the world and antimicrobial resistance has become a critical issue
^
5
^. In the last 20 years, treatment of typhoid fever with a 7-day course of a single oral antimicrobial, such as ciprofloxacin, cefixime or azithromycin, given in an out-patient setting has led to patient recovery in 4 to 6 days without the need for expensive hospitalization. Increasing antimicrobial resistance in Asia and sub-Saharan Africa threatens the effectiveness of these treatments and increases the risk of prolonged illness and severe disease.

The fluoroquinolone class of antimicrobials have been a common choice to treat typhoid fever across South Asia during the last two decades. Now low and high-level resistance is so widespread that the entire class is no longer a reliable treatment choice
^
2,
6
^. Cefixime and azithromycin are commonly recommended alternatives and widely used
^
7–
11
^, but the conflicting results from small randomised controlled trials (RCTs) with cefixime and azithromycin in typhoid fever leave many clinicians unsure about the optimum antimicrobial treatment for typhoid fever in this region.

The outcome for patients treated with cefixime (10–20mg/kg/day for 7–14 days) in typhoid fever are particularly mixed with prolonged fever clearance times of 6–8 days, clinical failure rates of between 6% and 27% and microbiological failure rate between 0% and 4.5%
^
12–
15
^. The reported fever clearance times with azithromycin treatment (10–20 mg/kg/day for 5–7 days) is usually 4–6 days and clinical failure rates range from 0% to 18% with a microbiological failure rate from 0% to 3.2%
^
7,
16–
23
^. A number of the studies with azithromycin have demonstrated a delayed microbiological clearance, indicated by positive blood culture during the treatment course
^
17,
19–
21,
23
^. Azithromycin activity is predominantly intracellular with studies from Vietnam indicating that up to one third of
*S.* Typhi may be found in the extracellular compartment
^
24,
25
^. The low levels of azithromycin in plasma may be insufficient to ensure adequate killing activity
^
26
^. In contrast, the extended-spectrum cephalosporin cefixime is predominantly active in the extracellular compartment although
*in-vitro* evidence also suggests some intracellular activity
^
27
^. The relative lack of intracellular activity by cefixime may be one reason for the variable treatment results and prolonged fever clearance times in patients with typhoid infection. For each of these antimicrobials, the exposure of the extracellular or intracellular bacteria to sub-therapeutic drug levels will increase its likelihood of resistance emergence.

### Rationale for the Azithromycin Cefixime Trial (ACT): an RCT in South Asia

We hypothesize that a combined treatment with azithromycin, active mainly intracellularly, and cefixime, active mainly extracellularly, will be a better option for the treatment of suspected and culture-confirmed typhoid fever in South Asia. There is some clinical evidence for this. The clinical response to treatment in 37 Israeli travellers returning from Nepal with paratyphoid fever was significantly better when azithromycin was combined with ceftriaxone in comparison to ceftriaxone alone with the fever clearance times reduced from six to three days
^
28
^. In an RCT of 105 adults with confirmed typhoid fever in Nepal, a combination of azithromycin and cefixime for out-patients and azithromycin and ceftriaxone for in-patients was superior to azithromycin alone with shorter fever clearance times
^
17
^. Unpublished data suggests that there is no evidence for significant antagonism against
*S*. Typhi
*in-vitro* with the combination of azithromycin and ceftriaxone/cefixime ([name], unpublished data,
Table 1).

**Table 1. T1:** *In-vitro* antimicrobial interactions between azithromycin and cefixime for recent clinical blood culture isolates of
*S*. Typhi.

Antimicrobial	Checkerboard assay, n (%) Total 100 isolates			Time kill assay, n (%) Total; 50 isolates		
	Synergy	Indifference	Antagonism	Synergy	Indifference	Antagonism
Azithromycin – ceftriaxone	14 (14)	85 (85)	0	12 (24)	34 (68)	4 (8)
Azithromycin – cefixime	6 (6)	94 (94)	0	8 (16)	38 (76)	4 (8)

### Study design

This is a phase IV, international multi-centre, multi-country, comparative participant and observer-blind, 1:1 randomised clinical treatment trial. Patients with suspected uncomplicated typhoid fever will be randomised to one of the two interventions: Arm A: azithromycin 20mg/kg/day oral dose once daily (maximum 1gm/day) AND cefixime 20mg/kg/day oral dose in two divided doses (maximum 400mg bd) for 7 days, Arm B: azithromycin 20mg/kg/day oral dose once daily (max 1gm/day) for 7 days AND cefixime-matched placebo for 7 days. The drug dosing table can be found as extended data
^
29
^. The ACT-South Asia study aims to compare a combination of azithromycin and cefixime with azithromycin alone in the outpatient treatment of clinically suspected and confirmed uncomplicated typhoid fever. We will recruit 1500 patients across sites in Bangladesh, India, Nepal and Pakistan. A placebo (sugar pill) will be used instead of cefixime in the single drug arm so that neither the patient nor the study team know which patient is receiving which treatment. We will assess whether treatment outcomes are better with the combined treatment after one week and at one and three month follow-up. 

## Protocol

This trial was registered on clinicaltrials.gov on the 16
^th^ April 2020 (NCT04349826). This protocol has been written according to the SPIRIT guidelines
^
29
^.
Figure 1 shows the study flowchart.

**Figure 1. f1:**
[figure not shown]
Trial schema. RDT= Rapid diagnostic test; CRP=C-reactive protein; PCR=polymerase chain reaction; COVID-19=coronavirus disease 2019; CMA=community medical auxiliaries

### Objectives

**
*Primary objective*
**

To determine whether combined treatment with seven days of an azithromycin and cefixime is superior to seven days of azithromycin and placebo in preventing treatment failure in patients with clinically suspected or confirmed uncomplicated typhoid fever.

**
*Secondary objectives*
**

To compare the fever clearance time (FCT) in patients in each treatment armTo compare the time from onset of treatment to treatment failure in patients in each treatment armTo compare the time from onset of symptoms to treatment failure in patients in each treatment armTo compare the occurrence of adverse events in each treatment armTo compare the clearance of faecal carriage of
*S*. Typhi or
*S.* Paratyphi in the patients with blood culture confirmed typhoid fever at onset in each treatment armTo compare the cost-effectiveness of the treatment in each treatment arm

**
*Exploratory objectives*
**

To determine the pharmacokinetics of each drug in the two treatment armsTo determine the diagnosis in participants who do not have blood culture confirmed typhoid feverTo compare the faecal micro biome of patients with confirmed and suspected typhoid fever

**
*Endpoints*
**

*Primary endpoint*

A composite outcome of treatment failure by the 28th day after the initiation of treatment will be defined by either of the following events: 1.Clinical failure: persistence of fever on day 7 (168 h) post treatment initiation OR The need for rescue treatment as judged by the Trial Clinician OR The development of any complication (e.g., clinically significant bleeding, fall in the Glasgow Coma Scale score, perforation of the gastrointestinal tract) OR Syndromic enteric fever relapse within 28 days of initiation of treatment. 2.Microbiological failure: a positive blood-culture for
*S.* Typhi or
*S*. Paratyphi on day 7 of treatment regardless of the presence of fever (microbiological failure) OR blood culture-confirmed typhoid fever relapse within 28 days of initiation of treatment.

*Secondary endpoints*

1. The fever clearance time (FCT) will be the time from the first dose of a study drug until a temperature of < 37.5°C (axillary); < 38.0°C (oral) has been achieved for at least 48 hours

2. The time to treatment failure will be the time from the first dose of a study drug until an event occurs defined as a treatment failure

3. The time to treatment failure will be the time from the day of the first symptom until an event occurs defined as a treatment failure. As subjects are only under observation from the initiation of treatment onwards, they will be considered as left-truncated at that timepoint.

4. Adverse events will be graded (grade 3/4 adverse events, serious adverse events, adverse events of any grade leading to modification of study drug dose or interruption/early discontinuation)

5. Positive culture of faeces sample for
*S*. Typhi or
*S*. Paratyphi with timepoints explicitly stated.

6. The incremental cost-effectiveness ratio (ICER) will comprise of the total costs per case, real outpatient and in-patient costs, total direct and indirect costs for the family and healthcare system and health outcomes converted to disability adjusted life years (DALYs). The cost per DALY averted will be compared against multipliers of the gross domestic product (GDP)/capita in each of the four countries to establish the cost-effectiveness of the combination regimen.

7. Additional diagnostic tests on the samples collected from participants who do not have blood culture confirmed typhoid fever

8. Analysis of the faecal microbiome in collected faecal samples

*Assessment of endpoints*

Participants, or their family members, will be trained how to monitor the temperature and then contacted on a twice daily basis by telephone for monitoring and recording of temperature and enquiry using symptom checklist. Temperature and symptom logs will be maintained during the twice daily telephone calls to measure fever clearance time and when the patient is seen on day 7. Each enrolled subject will measure temperature either in the axillary area or orally and stick to one method and not interchange so the documentation will not be confusing. If there is persistence of fever and/or symptoms on day 7 the patient will be reassessed, rescue treatment administered if appropriate and the patient will be judged to be a treatment failure. In addition, adverse events or signs of any complication (using a check list) developing at any time will be closely monitored and patients will be referred to the hospital if necessary, under the supervision of one of the trial physicians.

Patients still febrile and unwell on or before day 7 will be reassessed. In case of treatment failure a decision to admit or continue treatment as an outpatient will be made by the site Principal Investigator (PI). The choice of antibiotics used for cases of treatment failure, will depend on the initial report of blood culture if positive or the prevailing antibiotic sensitivity patterns if negative. The site PI will decide if rescue treatment is required. This may be ceftriaxone 60–80 mg/kg once daily (Max 4gm od) or meropenem 10–20 mg/kg three times daily or 0.5–1gm three times daily for body weight ≥ 50kg) according to local guidelines and follow-up will continue (in hospital if necessary).

Severe or complicated typhoid fever will be defined if any of the following develop:

•   Clinically significant gastrointestinal bleeding

•   Fall in the Glasgow Coma Scale score (delirium, obtundation or coma)

•   Perforation of the gastrointestinal tract (confirmed at surgery)

•   Haemodynamic shock (systolic blood pressure < 90mmHg and/or diastolic blood pressure < 60 mmHg associated with tissue hypoperfusion

•   Myocarditis (tachycardia or bradycardia with an associated abnormality of the electrocardiogram (ECG) or ultrasound evidence of a pericardial effusion)

•   Hepatitis (indicated by jaundice and/or hepatomegaly with abnormal levels of aspartate aminotransferase (AST) (>10 × normal range) or alanine aminotransferase (ALT) (>10 × normal range))

•   Clinical diagnosis of cholecystitis (right upper quadrant pain and tenderness without evidence of hepatitis; ultrasound appearance consistent with cholecystitis)

•   Pneumonia (respiratory symptoms and new chest X-ray infiltrates)

A positive culture of
*S.* Typhi or
*S.* Paratyphi from blood collected on day 7, regardless of the presence of fever, will be judged to be treatment failure. Rescue treatment will be administered if necessary at the discretion of the site PI. Similarly, blood culture positive or syndromic relapse of typhoid fever during the follow-up through until day 28 will be judged a treatment failure and further treatment will be given under the guidance of the site PI. Participants will be followed-up approximately until resolution. If the illness is not resolved at that time of follow-up, an additional follow-up will be arranged

Faecal carriage of
*S.* Typhi or
*S.* Paratyphi in the patients who were blood /stool culture positive for these organisms at entry to the study will be determined at 7 days, 14 days, 28 days and 3 months to check for clearance. If faecal carriage is still present at the 3 month follow up visit the Site PI will decide the need for further follow-up and treatment.

We will collect data on health facility and household costs and loss of income during the illness and up to 28 days to enable a cost of illness analysis for typhoid fever in these settings, as well as a comprehensive economic evaluation of the treatment strategies. The difference in direct purchase costs of the treatment strategies in the four countries are modest (e.g. a full course of azithromycin in the four countries is ~$5, and an additional course of cefixime would also cost ~$ 5). Therefore when considering these costs alone, any clinical benefits associated with the combined regimen may imply that the combined regimen is cost-effective. The economic benefits of the combined regimen, however, may extend further to include other health facility and household costs averted as most people in the subcontinent do not have health insurance; demonstrating these will be useful for policy guidance. We will therefore collect data on health facility and household costs and loss of income during the illness and up to 28 days to enable a cost of illness analysis for typhoid fever in these settings, as well as a comprehensive economic evaluation of the treatment strategies. The analysis will take a societal perspective and include the costs of AMR per antibiotic consumed using methods from a recent publication on this topic
^
12
^. We will measure the incremental cost-effectiveness ratio (ICER) which will comprise of the total costs per case, real outpatient and in-patient costs, total direct and indirect costs for the family and healthcare system and health outcomes converted to Disability Adjusted Life Years (DALYs). The cost per DALY averted will then be compared against multipliers of the GDP/capita in each of the four countries to establish the cost-effectiveness of the combination regimen.

The end of trial is the point at which the last participant has completed their follow-up period, all the data has been entered and queries resolved, the last sample has been processed and the database locked.

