### Statistical and analytical plans

The statistical aspects of the study are summarised here with details fully described in a statistical analysis plan (SAP) which will be finalised before any analysis takes place. The primary endpoint of this trial is the composite outcome of treatment failure by the 28th day after the initiation of treatment. Subjects who withdraw from the study prior to day 28 without treatment failure will be treated as right-censored. The primary comparison of the absolute risk of treatment failure until day 28 between the treatment arms will be based on Kaplan-Meier estimates and corresponding standard errors according to Greenwood’s formula.

The time to treatment failure from the onset of treatment will be described using Kaplan-Meier curves and compared between the treatment arms with a Cox proportional hazards model with treatment assignment as the primary covariate and adjustment for blood culture result (positive for
*S.* Typhi or
*S.* Paratyphi vs. negative), age (children (<16 years) and adults (≥16 years)), and country. Time to treatment failure from symptom onset will be analysed in the same way but subjects will be considered as left-truncated at the time of onset of treatment to account for the fact that they were not under observation before that timepoint.

Fever clearance time will be calculated using temperatures recorded twice per day and treated as an interval-censored outcome. The fever clearance time distribution will be estimated using the non-parametric maximum likelihood estimator (NPMLE) and comparisons between the arms will be based on a parametric Weibull accelerated failure time model. 

A two-sided significance level of 5% will be applied to all efficacy analyses. The primary analysis population for all analyses is the modified intention to treat (ITT) population consisting of all patients who have been randomised to the trial and received at least one dose of study treatment. Analysis will be according to the randomized treatment arm. Subjects, who were mistakenly randomised or withdrew before the first dose of study treatment was given, will be excluded. Subjects who were unblinded will be included in the ITT population.

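### Left truncation at treatment start is not warranted for time from first symptom to treatment failure, and it can push the planned descriptive Kaplan-Meier curves above the true proportion failed

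*Protocol article*

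**What the plan says.** Objectives (Secondary endpoints, item 3) starts the clock on the day of the first symptom and ends it at treatment failure. The reason for truncating is "As subjects are only under observation from the initiation of treatment onwards", and the consequence is that "they will be considered as left-truncated at that timepoint".

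Statistical and analytical plans repeats the rule: "Time to treatment failure from symptom onset will be analysed in the same way but subjects will be considered as left-truncated". The analysis it refers back to is the one from treatment onset: "The time to treatment failure from the onset of treatment will be described using Kaplan-Meier curves", with the arms compared by a Cox model. On a plain reading, delayed-entry Kaplan-Meier curves and a delayed-entry Cox model are planned from symptom onset.

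The event is the primary composite: "A composite outcome of treatment failure by the 28th day after the initiation of treatment". Its components include "persistence of fever on day 7 (168 h) post treatment initiation" and "Syndromic enteric fever relapse within 28 days of initiation of treatment".

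**The concern.** Left truncation repairs a sample from which people are missing because their event came before observation could begin. The plan's reason is only that participants were not watched before treatment. That does not matter if the event cannot happen in that interval, and a failure of a treatment not yet started cannot.

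The method also needs entry time to be independent of event time. Here the two are tied together. A participant treated on symptom day 3 who is still febrile on treatment day 7 fails on symptom day 10; one treated on symptom day 10 fails on day 17.

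At stake is whether the published curves for a pre-specified secondary endpoint can be read as failure risks. If they cannot, they may disagree with the primary Kaplan-Meier risk in the same patients with the same events.

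**Working it through.** **Inputs from the Protocol article.** Failure risks are 15% and 9% (Sample size calculation). Fever lasts at least 72 hours and at most 14 days at entry (Study procedures, inclusion and exclusion criteria). The event definition is in Objectives. The plan states no figure for this endpoint. Its power figures do reproduce with 750 × 0.9 = 675 per arm: 92.5%, 79.4%, 93.8% and 77.4%, against the stated 92%, 80%, 94% and 77%.

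**Assumptions not in the documents.** These are the distribution of onset-to-treatment time within days 3 to 14, and the split of failures into before day 7, on day 7, and relapse. The 3 to 14 day limits apply to fever, whereas the clock starts at the first symptom, so the true spread could be wider.

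**Direction.** The curve is 1 − Π(1 − d/R), where d is the number of failures at a symptom day and R the number at risk. Truncation removes not-yet-treated participants from R and leaves d unchanged. Each step is therefore at least as large as without truncation. It is strictly larger whenever someone fails while another participant is still untreated. With no censoring, the untruncated curve equals the observed proportion failed.

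**Deterministic case.** Take twelve equal groups of size 1 entering on days 3 to 14, with 15% of each failing on treatment day 7. At symptom day t (10 to 21), the planned risk set is min(t − 3, 12) − 0.15(t − 10). The untruncated risk set is 12 − 0.15(t − 10).

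| Symptom day | Planned risk set | Planned curve | Untruncated risk set | Untruncated curve = truth |
|---|---|---|---|---|
| 10 | 7.00 | 2.1% | 12.00 | 1.25% |
| 14 | 10.40 | 8.5% | 11.40 | 6.25% |
| 21 | 10.35 | 17.0% | 10.35 | 15.0% |

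To day 14, the planned survival is (1 − 0.15/7.00)(1 − 0.15/7.85)(1 − 0.15/8.70)(1 − 0.15/9.55)(1 − 0.15/10.40) = 0.915. From day 15 both risk sets agree and the remaining factor is 10.20/11.25 = 0.907. The product is 0.830, so the curve ends at 17.0%. All failures fall by day 21, before any day-28 censoring, so this 2.0-point excess is due to truncation alone. With 9% failing, the planned curve ends at 10.3%.

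**Simulation.** There were 750 per arm, a true control risk of 15%, and 150 runs per scenario. The split gives the percentage of failures before day 7 / on day 7 / relapsing on days 8 to 28. Both final values include censoring at treatment day 28.

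| Entry | Split | Day 21: planned vs true | End: planned vs ordinary |
|---|---|---|---|
| All on day 5 | 20/60/20 | 13.2 vs 13.2 | 15.0 vs 15.0 |
| Days 3–7 | 0/80/20 | 13.2 vs 13.2 | 15.3 vs 15.3 |
| Days 3–7 | 40/40/20 | 14.4 vs 13.4 | 16.4 vs 15.4 |
| Skewed early | 0/80/20 | 13.3 vs 13.2 | 17.1 vs 17.0 |
| Skewed early | 40/40/20 | 14.1 vs 13.1 | 17.7 vs 16.8 |
| Uniform whole days 3–14 | 0/80/20 | 14.5 vs 12.9 | 17.5 vs 15.9 |
| Uniform whole days 3–14 | 5/85/10 | 16.2 vs 14.0 | 17.6 vs 15.4 |
| Uniform whole days 3–14 | 40/40/20 | 16.9 vs 12.7 | 19.9 vs 15.8 |

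A larger check (300,000 participants) used uniform whole-day entry, a third of failures before day 7 on a half-day grid, and 20% relapsing. It gave 11.3% against a true 6.5% at symptom day 14, and 17.3% against 12.7% at day 21, an excess of just under 5 points.

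**Separating censoring.** Participants without failure leave the risk set at entry + 28 days, so the earliest such exit is symptom day 3 + 28 = 31. Before then the ordinary curve matches the true proportion. After it, the ordinary curve also rises above 15%, as the last column shows.

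**Treatment effect.** Simulated Cox hazard ratios were 0.561 from treatment start, 0.560 from symptom onset with truncation and 0.561 without it.

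**The case against.** Delayed entry is a conventional choice when the clock starts before observation, and the stated objective is to compare the arms. The Cox model does that, and its hazard ratio does not move. The Kaplan-Meier curves only describe, and their use here is inferred from the cross-reference to the treatment-onset analysis. All of this stands and limits the point to the curves.

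Complications form part of the composite, and patients who already show bleeding, obtundation, shock or other severe signs are excluded (Study procedures). Entry is thus conditional on not yet having had such an event, which gives truncation some basis. But the plan treats those conditions as reasons for exclusion, and its composite runs from initiation of treatment. They are not treatment failures under its own definition.

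An ordinary curve also has a cost. It counts a guaranteed event-free stretch before treatment, so its shape depends on how late this sample presented. That is fair, but it is what the endpoint as defined measures.

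A reader might infer that the whole gap between the planned curve's final value and 15% comes from truncation. It does not: with early-skewed entry and a 0/80/20 split, the planned curve ends at 17.1% and the ordinary one at 17.0%. A reader might also infer that the treatment comparison or the primary result is compromised. The hazard ratios above rule out the first, and the primary analysis runs from treatment initiation without truncation.

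**Conclusion.** The point holds for the descriptive Kaplan-Meier curves from symptom onset. No failure is truncated, entry and failure time are dependent by construction, and the delayed-entry curve cannot be lower than the true proportion failed.

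On a 15% risk, the excess from truncation alone is about 0 if entry clusters on days 3 to 7 and no failures precede treatment day 7. With few or no failures before day 7 it stays within about 2 points for early-skewed or uniform entry. It reaches about 5 points with uniform entry over days 3 to 14 and a third of failures before day 7. Only the direction is certain. The size rests on entry and failure-time distributions that the document does not give.

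The further rise after about symptom day 31 comes from day-28 censoring and would remain without truncation. The importance is low: one secondary endpoint's curves are affected, while the hazard ratio and the primary analysis are essentially unchanged.

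**What to change.** In Objectives (Secondary endpoints, item 3) and Statistical and analytical plans, remove the left-truncation rule for the descriptive curves. State that participants are failure-free by definition from first symptom to first dose, and plan an ordinary Kaplan-Meier curve from symptom onset. Read that curve only up to the symptom day at which day-28 censoring begins (about day 31 if the shortest onset-to-treatment time is 3 days). Take the 28-day failure risk from the primary analysis.

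The Cox comparison can stay on its planned time scale. Moving it to time from first dose with symptom duration as a covariate would be a preference, and would abandon this endpoint's own clock.

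The cost is a wording change. The first-symptom date is already needed for the endpoint, so no new data are required. The small downside is that the curve reflects this sample's delay in presenting as well as its failures, which a footnote can say.
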